*Measures and data collection*. Each RE-AIM measure below, using data collected from aims 1–3, will be calculated for both the IU and GTO groups:*Reach*—Obtained from aim 1, the Reach measure will be the percent of all eligible Veterans who receive MISSION-Vet with adequate fidelity (defined as the endorsement of at least 75 % of the items on the MISSION-Vet Fidelity measure).*Effectiveness*—Obtained from aim 3, effectiveness will be the percentage of all eligible Veterans *who receive MISSION*-*Vet with adequate fidelity* who improve on each outcome in an amount consistent with a statistically significant effect.*Adoption*—The proportion of case managers who have more than 50 % of their eligible Veterans engaged in MISSION-Vet will be judged to have “adopted” MISSION-Vet as a standard protocol for Veterans with mental illness and co-occurring substance abuse disorders.*Implementation*—The extent to which the MISSION-Vet intervention was well implemented will come from aim 1 and be expressed as the percentage of eligible Veterans who actually participated in MISSION-Vet who had adequate fidelity (endorsement of at least 75 % of the items on the MISSION-Vet Fidelity measure).*Maintenance*—The degree to which the successful deployment of MISSION-Vet was maintained will come from data collected through the previous components of the RE-AIM model but extended a year beyond the end of the GTO support. Thus, this study will be able to assess whether MISSION-Vet maintains a high Reach, Effectiveness, Adoption, and Implementation between the end of the GTO support and the last data collection wave, which will be a year after the GTO support ends.

*Hypothesis*. We expect better results across all elements of the RE-AIM model in the GTO group than in the IU group.

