*Data analysis*. The scores for R, E, A, and I will be calculated among the Veterans in both the GTO and IU groups during the 2-year period of GTO support. For *Reach*, we will perform a *z* test for the comparison of the proportion of Veterans at the end of the GTO period with adequate fidelity between GTO versus IU. The *Effectiveness* analysis will involve *t* tests comparing mean scores at the end of the GTO period for the proportion of time housed and homeless (on the logit scale), components of the ASI, and the GAF. For *Adoption*, we will compare the proportion of case managers through a *z* test who have “adopted” MISSION-Vet according to the specified measure. We will also perform a logistic regression of whether a case manager adopted MISSION-Vet as a function of study arm, one of the moderating variables, and their interaction, testing specifically for the interaction term. The analysis of *Implementation* will compare through a *z* test the proportion of Veterans who participated in MISSION-Vet who had a fidelity score of at least 75 % between the GTO versus IU groups.

*Maintenance*—The analyses described above for R, E, A, and I will be similarly applied to the data collected and summarized a year after the end of the GTO support period.

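### Maintenance is defined as keeping a high level from the end of GTO support to one year later, but its only stated analysis compares GTO with IU at the later date and does not show whether the level was kept

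*Protocol article*

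**What the plan says.** All statements are in the protocol article, in the section on Aim 4 (RE-AIM).

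- **Measure.** "The degree to which the successful deployment of MISSION-Vet was maintained will come from data collected through the previous components of the RE-AIM model", extended by a year after support ends. On that basis, "this study will be able to assess whether MISSION-Vet maintains a high Reach, Effectiveness, Adoption, and Implementation between the end of the GTO support"; the second date is the final wave, one year on.
- **Hypothesis.** "We expect better results across all elements of the RE-AIM model in the GTO group than in the IU group". Maintenance is one of those elements.
- **Analysis of Maintenance.** One sentence: "The analyses described above for R, E, A, and I will be similarly applied to the data collected and summarized a year after". The date meant is one year after support stops.
- **The analyses carried over.** Reach: "test for the comparison of the proportion of Veterans at the end of the GTO period with adequate fidelity between GTO versus IU" (a z test). Implementation uses a z test of the proportion of participating Veterans who "had a fidelity score of at least 75 % between the GTO versus IU groups". Effectiveness uses t tests of mean scores at one date. Adoption uses a z test on case managers plus a logistic regression for moderation by arm. All of these set GTO against IU at one date.

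The introduction to the measures says that all of them are collected for three years, the third to assess sustainability. The Power analysis section calls Aim 4 exploratory and gives no power for it.

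**The concern.** The stated question runs over an interval: was a high level still high a year after support stopped? Answering it needs the value at both ends. The stated analysis uses the later date only. Its null hypothesis is that the arms are equal one year after support. That is a different statement from saying that an arm kept its level.

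The two can part company. An arm that led clearly at the end of support can lose much of its Reach and still be ahead of the other arm a year later. If that result is reported under the name Maintenance, a reader may take it to say that MISSION-Vet was sustained in the GTO sub-teams. The sustainability conclusion is the declared purpose of the third year of data, so it should rest on a quantity that measures sustainability.

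**Working it through.** **1. Sample size used for illustration.** The article gives no figure for Maintenance, so there is none to reproduce. The effective sample for Aim 1 (Power analysis section) was checked first:

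- 2110 × 0.80 × 0.95 = 1603.6 (stated 1604)
- Deff = 1 + (24.3 − 1) × 0.15 = 4.495 (as stated)
- 1604 / 4.495 = 356.8 (stated 356), so 178 per arm
- Smallest detectable effect with 178 per arm, two-sided 0.05, 80% power: 0.298 (as stated)

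Using 178 per arm already discounts for clustering by case manager at the plan's ICC of 0.15.

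**2. Assumed rates.** The article gives no Reach rates. Assume GTO 40% at the end of support and 30% a year later, and IU 20% at both dates. Only GTO loses ground.

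**3. The stated test at one year.** Pooled two-proportion z test, 30% v 20%, 178 per arm, two-sided 0.05:

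- Pooled rate 0.25; SE under the null = √(2 × 0.25 × 0.75 / 178) = 0.0459
- Critical difference = 1.96 × 0.0459 = 0.0900
- SE under the alternative = √((0.30 × 0.70 + 0.20 × 0.80) / 178) = 0.0456
- Probability of favouring GTO = Φ((0.10 − 0.0900) / 0.0456) = Φ(0.22) = 0.587; simulation of the test gives 0.59

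The values 40% and 20% at the end of support enter nowhere in this calculation.

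**4. What both dates would show.** Treating the dates as independent (a simplification), with the same 178 per arm:

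- GTO change = −10 points; SE = √((0.40 × 0.60 + 0.30 × 0.70) / 178) = 0.0503; 95% CI −19.9 to −0.1
- IU change = 0 points; SE = √(2 × 0.20 × 0.80 / 178) = 0.0424; 95% CI −8.3 to +8.3

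Shown beside the levels, these would tell the reader that GTO is still ahead and has fallen.

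**5. A more extreme assumed case.** GTO 60% to 15%, IU 5% at both dates. At one year, Z = 0.10 / √(2 × 0.10 × 0.90 / 178) = 3.14, p = 0.0017 in favour of GTO, although GTO kept a quarter of its Reach (15/60).

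**6. Why change alone is not the answer either.** Take GTO 40% to 30% and IU 20% to 10%.

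- Absolute scale: both arms lose 10 points, and a comparison of change rejects about 5% of the time.
- Relative scale: GTO keeps 75% (30/40) and IU keeps 50% (10/20).
- Logit scale: an arm-by-time test favours GTO about 15% of the time (dates independent).

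The same data support different statements on different scales, so the scale has to be named in advance.

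**The case against.** The strongest reply is that the one-year contrast is the right test of the stated hypothesis. That hypothesis is between arms, and the randomised comparison a year after support shows whether GTO's advantage outlasts the support. It also uses new data and can detect a lost advantage: with GTO falling from 40% to 20% and IU flat at 20%, it favours GTO only about 2.5% of the time. This stands, and it is why the contrast should be kept.

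It also stands that the article speaks of maintaining a high level and never defines Maintenance as change. A difference in change penalises the arm that started higher: an IU arm steady at 5% would look better than a GTO arm going from 60% to 50%. Replacing the planned test with an arm-by-time test would therefore swap one imperfect measure for another.

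Two stronger readings are tempting, and the article supports neither. One is that the test would credit GTO when nothing at all was maintained. It would not, because a significant result needs GTO activity above IU at the later date. The other is that failing to reject when both arms hold the same level is a defect. It is not: GTO is then no better than IU, and a comparison of change would not reject either.

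Finally, an article condenses a fuller plan, and the measures are computed in both arms at both dates, so a descriptive reading is possible. That lowers the stakes. But the Maintenance analysis is stated, not left out, and as stated it does not use the earlier date that the question needs.

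**Conclusion.** The point holds in a limited form. The stated Maintenance analysis validly addresses whether GTO still exceeds IU one year after support. It does not address whether the level of Reach, Effectiveness, Adoption and Implementation was kept, which is how the measure is described.

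Under the assumed 40% to 30% in GTO and flat 20% in IU, with 178 effective Veterans per arm, the test favours GTO about 59% of the time. That figure rests on assumed rates, a two-sided 0.05 level and the Aim 1 effective sample carried over to Reach at one year. It shows that the two questions can come apart; it does not predict a result.

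A reader might infer that the third year would merely repeat the end-of-support finding, or that the planned contrast is invalid. Neither follows. The consequence is modest because Aim 4 is exploratory, but the correction is cheap and worth making.

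**What to change.** In the Aim 4 data analysis paragraph on Maintenance:

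1. Keep the GTO-versus-IU comparison one year after support and label it *sustained difference between arms*.
2. For each RE-AIM measure and each arm, report the level at the end of support and one year later, and the within-arm change between the two dates with a 95% CI that allows for clustering.
3. Base the statement on maintenance on the levels, the within-arm changes and the sustained difference together.
4. If a between-arm comparison of change is reported, treat it as supportive, name its scale (for example the absolute risk difference), and read it beside the end-of-support level.

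The cost is a little more analysis and wider intervals for change than for a single-date level. In the illustration, the half-width for GTO Reach is 9.9 points for the change (dates independent), against 1.96 × √(0.30 × 0.70 / 178) = 6.7 points for the one-year level. No new data collection is needed, and Aim 4 has no stated power to lose.

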### Power analysis

We demonstrate that for aims 1, 2, and 3, we will have at least 80 % power to detect intervention effects at the 0.05 significance level (aim 4 is exploratory and thus we are not able to calculate power for that aim). Our power calculations were performed using the power analysis software G*Power 3.1.2 [49]. Previous studies examining the effect of GTO used different measures than in the current study. We therefore assumed effect sizes based on a previous study of the effect of GTO on capacity to carry out evidence-based drug abuse prevention programming. The measures used in that study were of provider knowledge (effect size = 0.21 after 2 years of GTO), attitudes (effect size = 0.38 at 1 year of GTO and 0.59 at 2 years of GTO), and skills (effect size = 0.07 at 1 year of GTO and 0.28 at 2 years of GTO) all related to the performance of practices associated with evidence-based prevention programming [16]. These measures are relevant because GTO will attempt to impact knowledge, attitudes, and skills in the proposed study as well, but in this case around the use of MISSION-Vet. We use these values as a rough guide for the effects we might expect to detect for the current study, along with conventional effect size interpretations.

For aims 2 and 3, we will focus on the subsample of Veterans in the study for whom we have 12 months of data collected over consecutive 3-month intervals. Because these Veterans serve as their own controls relative to time, they provide the greatest power in detecting the effect of MISSION-Vet + GTO. With the same design effect as in aim 1, the effective sample size available for aims 2 and 3 controlling for clustering is 356 Veterans. For a linear repeated measures model with two treatment groups and five measurements per unit (that is, one every 3 months for a year, including baseline), and assuming a sample of 356 units to randomly divide approximately equally between the two groups, the time-by-intervention effect size that can be measured with 80 % power is 0.082. By convention, this is considered a very small effect size, and it is also small compared to the ones found above in the drug abuse prevention study. We therefore anticipate detecting effects with sufficient power for aims 2 and 3.

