#### Recruitment

The subjects in this study are the HUD-VASH case managers although data about the Veterans on their caseload will also be collected. All case managers were invited to participate and consented before randomization by the study staff. The two sub-teams from each site that were assigned to GTO or IU have approximately equal numbers of case managers and vouchers, although the exact numbers shift frequently due to staff turnover and Veteran dropout, graduation, and the issuing of new vouchers. Regardless, consistent with cluster random assignment, each case manager is linked to a certain sub-team (and thus study condition), and each Veteran is in turn linked to a specific case manager. If sites decide to add new staff to a sub-team, that case manager would then automatically be assigned to the condition of that sub-team.

All HUD-VASH case managers in both groups will be invited to the webinar training on MISSION-Vet. After MISSION-Vet begins, case managers will be responsible for engaging their Veterans into MISSION-Vet services. Any Veteran participating in HUD-VASH at each of these three sites is eligible to receive MISSION-Vet services. Through training and TA, case managers and peer specialists will be guided to follow the recommended inclusion and exclusion criteria of MISSION-Vet: (1) has a current substance abuse or dependence disorder and a co-occurring mental illness and (2) is willing to participate in MISSION-Vet services. However, the decision with whom to deliver MISSION-Vet will ultimately be made by the case managers. MISSION-Vet takes about 1 year to fully deliver; therefore, Veterans will be invited to take part in MISSION-Vet in the first year of the 2-year intervention period. The study received a waiver of consent to use client-level data already being collected as part of the homeless data program management system of HUD-VASH.

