#### Aim 2: compare the effect on the proportion of time the Veteran is housed between GTO and IU groups

*Data sources*. Veterans served by case managers in the GTO and IU groups.

*Measures and data collection*. For each Veteran entering HUD-VASH, a case manager must complete a HUD-VASH Referral Worksheet that contains the program’s first assessment of days of homelessness and housing. Then, case managers provide data every 3 months on the number of days housed in the last 90 days using the Housing Progress Report form. Case managers are also required to report when a Veteran loses their housing voucher each month. These reports are stored in national database called HOMES (Homeless Operations, Management and Evaluation System).

*Hypothesis*. We expect that Veterans assigned to case managers in the GTO group, who receive MISSION-Vet, will have more days housed in the prior 3 months compared to Veterans who receive MISSION-Vet from case managers in the receiving IU group.

*Data analysis*. Again, we will fit repeated measures linear random effects models in this analysis. As a secondary analysis, we will perform a *z* test for the comparison of the proportion of Veterans at the end the study who have retained their housing (versus lost their voucher) between GTO versus IU.

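### The power section confines Aims 2 and 3 to Veterans with a complete 12-month series, a post-randomisation selection that can bias the GTO-IU comparison, and gives that subsample the full-sample effective size

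*Protocol article*

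**What the plan says.** The Power analysis section of the protocol article names the Veterans on whom Aims 2 and 3 will rest: "we will focus on the subsample of Veterans in the study for whom we have 12 months of data collected over consecutive 3-month intervals". The reason follows: "Because these Veterans serve as their own controls relative to time, they provide the greatest power in detecting the effect of MISSION-Vet + GTO". It then states that "the effective sample size available for aims 2 and 3 controlling for clustering is 356 Veterans", and that with five quarterly measurements, counting baseline, "the time-by-intervention effect size that can be measured with 80 % power is 0.082".

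The Aim 2 and Aim 3 sections specify repeated measures linear random effects models. They neither repeat the restriction nor say what happens to Veterans with incomplete series.

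Under Aim 2, days housed come from a form that the case manager completes every 3 months. Voucher loss is recorded separately: "Case managers are also required to report when a Veteran loses their housing voucher each month". A secondary z test compares the proportions who kept housing rather than losing the voucher at the end of the study. The Recruitment section expects movement on and off caseloads: "the exact numbers shift frequently due to staff turnover and Veteran dropout, graduation, and the issuing of new vouchers".

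**The concern.** Whether a Veteran has five consecutive quarterly records is known only after randomisation. The housing form and the Aim 3 ratings are both completed by the Veteran's case manager, so a Veteran who leaves the caseload during the year probably has no full series. One route out is voucher loss, which the protocol treats as a housing outcome. GTO is expected to improve housing, so the share with a full series, and the kind of Veteran who has one, may differ between arms. A comparison of complete cases then no longer compares the randomised sub-teams. At stake are the main models of two of the three aims for which power is claimed.

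The power section also treats the subsample as if it were the whole sample. Nothing is deducted for Veterans without 12 months of data.

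**Working it through.** **1. Reproducing the stated figures.** Inputs from the Power analysis section: 2110 vouchers, reductions of 20 % and then 5 %, 66 case managers, ICC 0.15.

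- Veterans: 2110 × 0.80 × 0.95 = 1603.6 (stated 1604).
- Veterans per case manager: m = 1604 / 66 = 24.3.
- Design effect: 1 + (24.3 − 1) × 0.15 = 4.495.
- Effective size: 1604 / 4.495 = 356.8 (stated 356). A stray 265 is printed beside it, but the later figures use 356 and nothing here depends on 265.
- Detectable time-by-intervention effect: noncentral F test with λ = f² × N × 5 / (1 − ρ), df 4 and 4(N − 2) = 1416, sphericity assumed. With N = 356 and correlation between repeated measures ρ = 0, f = 0.0820 (stated 0.082). With ρ = 0.5 it would be 0.058.

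The figures reproduce, but only with all 1604 Veterans complete. The two reductions cover absence of a co-occurring substance use disorder and case manager refusal. Neither covers Veteran exit or missing forms.

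**2. Effective size of a real subsample.** The complete share c is an assumption, since the article gives none. The recalculated form uses m = 24.3c, Deff = 1 + (m − 1) × 0.15 and effective N = 1604c / Deff. The alternative keeps Deff at 4.495, because the text says the Aim 1 design effect is reused. Detectable f is at ρ = 0.

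| Complete share | Veterans | Recalculated Deff | Effective N | f | Effective N, Deff 4.495 | f |
|---|---|---|---|---|---|---|
| 90 % | 1444 | 4.131 | 349 | 0.083 | 321 | 0.086 |
| 80 % | 1283 | 3.766 | 341 | 0.084 | 285 | 0.092 |
| 70 % | 1123 | 3.402 | 330 | 0.085 | 250 | 0.098 |
| 60 % | 962 | 3.037 | 317 | 0.087 | 214 | 0.106 |
| 50 % | 802 | 2.673 | 300 | 0.089 | 178 | 0.116 |

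The recalculated columns are the coherent ones, because fewer Veterans per case manager means a smaller design effect.

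**3. What selection can do to days housed.** All rates here are assumed. They show a mechanism and do not estimate its size. Suppose 10 % of GTO and 15 % of IU Veterans leave through voucher loss and lack a full series, with a last-quarter mean of 85 days for those who stay and 20 for those who leave.

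- All Veterans: GTO 0.90 × 85 + 0.10 × 20 = 78.5; IU 0.85 × 85 + 0.15 × 20 = 75.25; difference +3.25 days.
- Complete cases: 85 − 85 = 0. This zero is built in by giving stayers the same mean in both arms.
- If the extra 5 % kept under GTO average 70 days: all Veterans 0.85 × 85 + 0.05 × 70 + 0.10 × 20 = 77.75, difference +2.5; GTO complete cases (0.85 × 85 + 0.05 × 70) / 0.90 = 84.2, difference −0.8.
- If the exit rates are exchanged (GTO 15 %, IU 10 %): all Veterans −3.25, complete cases 0, so a harm is hidden.

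Benefit or harm can be hidden, and the sign can change. Graduates and late entrants, who are not modelled here, would also be removed.

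**4. The power reason.** A Veteran with two or more quarters is also his or her own control over time. A linear random effects model uses those quarters. A complete series carries more information per Veteran than a partial one, but discarding the partial ones adds none.

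**The case against.** The strongest reply is that the sentence belongs to a power calculation that needed a balanced five-measurement layout, while the Aim 2 and Aim 3 analysis paragraphs carry no restriction and name models that accept incomplete series. That stands in part: the article does not settle that the analysis itself is confined to complete cases. But the wording announces an intention, it is the only description of the analysis set for these aims, and nothing elsewhere overrides it. The sections need reconciling.

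A reader might go further and infer that every Veteran who loses a voucher is removed, so that a true GTO benefit is necessarily erased. The article does not support this. It nowhere says that quarterly reports stop at voucher loss or that voucher loss ends case management. A Veteran who spends part of a quarter unhoused but is still reported on stays in, as does one who loses the voucher after month 12. Graduates and late entrants drop out as well, so the direction of bias is open.

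Voucher loss is not ignored either. The secondary z test compares it by arm with no stated restriction and recovers some of the lost information, but it does not repair the main Aim 2 model or any Aim 3 model. The sample-size error is also modest once the design effect is recalculated. Aim 1 is untouched, and the trial places its emphasis on the implementation strategy.

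**Conclusion.** The point holds in a limited form. As written, the power section directs Aims 2 and 3 to a subsample defined after randomisation and plausibly linked to the Aim 2 outcome, for a power reason that does not hold. The resulting bias cannot be sized or signed from the article, which gives no exit rates. The link between exit and missing quarterly records is a reasonable inference, not a documented fact.

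Giving the subsample an effective size of 356 is wrong as written, since it requires 100 % completeness. At an assumed 50-90 % complete, and with the ICC of 0.15 and ρ = 0 that the stated figures imply, the effective size is about 300-349 and the detectable effect about 0.083-0.089 instead of 0.082. That alone would not change the claim of adequate power. Selection is what needs correcting.

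**What to change.** - Reconcile the Power analysis section with the Aim 2 and Aim 3 analysis paragraphs. State that the planned repeated measures random effects models are fitted to all available quarters, for all Veterans in the target population of those aims, by randomised sub-team.
- Keep the complete-series subsample as a sensitivity analysis only.
- State that the all-available-data model assumes data are missing at random. For Aim 2, add a sensitivity analysis that uses the recorded voucher losses, for example counting days after a loss other than graduation as not housed. This is a strong assumption, since a Veteran may be housed without a voucher, so it should not be the main analysis.
- Restate the effective size and detectable effect, either for the expected complete share or for the all-available-data set, with the assumed share given.

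The cost is revised wording, a little more analysis on data already reported to HOMES, and a slightly less favourable power figure. No new data collection is needed.

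### The 0.082 detectable effect for aims 2 and 3 fits Cohen's f but is compared with effects the plan handles as mean differences, and its N of 356 comes from the full sample

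*Protocol article*

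**What the plan says.** The Power analysis section of the protocol article opens by promising "at least 80 % power to detect intervention effects at the 0.05 significance level" for aims 1, 2 and 3, and names its tool: "Our power calculations were performed using the power analysis software G*Power 3.1.2". It lists five effects from an earlier GTO study as a rough guide: knowledge 0.21 (2 years), attitudes 0.38 (1 year) and 0.59 (2 years), and skills 0.07 (1 year) and 0.28 (2 years).

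For aim 1, an expected 1604 Veterans are divided by a design effect of 4.495 to give 356. The detectable effect by a two-sample t test is 0.298. That figure is set against the earlier study's effects and the 0.2/0.5 conventions for small and medium.

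For aims 2 and 3 the analysis is limited to the subsample with 12 months of data. The stated reason is: "Because these Veterans serve as their own controls relative to time, they provide the greatest power". With the aim 1 design effect carried over, "the effective sample size available for aims 2 and 3 controlling for clustering is 356 Veterans". The calculation is for "a linear repeated measures model with two treatment groups and five measurements per unit", "assuming a sample of 356 units to randomly divide approximately equally between the two groups", and the result is that "the time-by-intervention effect size that can be measured with 80 % power is 0.082". Neither the metric nor a within-person correlation is given. The text continues: "By convention, this is considered a very small effect size, and it is also small compared to the ones found above", and from this it infers that power for aims 2 and 3 is sufficient.

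**The concern.** An effect size of 0.082 looks far better than the 0.298 quoted for aim 1 from the same effective N. Repeated measures can sharpen a comparison, but a gain of that size should prompt a check of the scale. G*Power's repeated-measures interaction routine works in Cohen's f. The aim 1 figure and its 0.2/0.5 benchmarks are on the mean-difference scale, and the earlier GTO effects are set beside them. If 0.082 is an f, it cannot be ranked against 0.07 to 0.59 without conversion.

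Aims 2 and 3 cover housing and all the clinical outcomes. The claim of ample power rests on this comparison, and the Design challenges section relies on the power analyses when it discusses staff turnover. A null result could be read as excluding very small effects when the calculation shows no such thing.

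Separately, an effective N derived from every Veteran in aim 1 should not be unchanged in an analysis restricted to those with a full year of data.

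**Working it through.** **Inputs from the article (Power analysis).** Alpha 0.05, power 80 %, k = 2 groups, m = 5 measurements, N = 356, about 1:1 allocation. Full sample 1604, 66 case managers, ICC 0.15, design effect 4.495. Earlier effects 0.07, 0.21, 0.28, 0.38, 0.59.

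**1. Reproduce aim 1.** 2110 × 0.8 × 0.95 = 1603.6, and 1604/4.495 = 356.8. A two-sample t test with 178 per arm detects 0.298 with 80 % power, as stated.

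**2. Reproduce 0.082.** For the within-between interaction, the noncentrality is λ = f²·N·m/(1 − ρ), with df1 = (k − 1)(m − 1) = 4 and df2 = (N − k)(m − 1) = 354 × 4 = 1416, under sphericity. With ρ = 0 and f = 0.082, λ = 0.006724 × 356 × 5 = 11.97 and power is 0.7998. The stated figure is therefore Cohen's f under these inputs.

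This input set is not unique. Relaxing sphericity, epsilon 0.75 with ρ 0.18, 0.5 with 0.38, or 0.25 with 0.62 also gives 0.082 at N = 356. The article states neither quantity.

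**3. Could 0.082 be a mean difference?** No. A 12-month difference of 0.082 SD with 178 per arm has about 12 % power by t test, and about 7 % by the same interaction test (ρ = 0, linear divergence).

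**4. Convert f to a 12-month difference D (SD units, equal baselines).** With two equal arms, f is half the SD, over the five visits, of the between-arm difference.
- Linear divergence (0, ¼, ½, ¾, 1)·D: SD = 0.3536·D, so f = 0.1768·D and D = 0.082/0.1768 = 0.46.
- Step after baseline (0, 1, 1, 1, 1)·D: SD = 0.4·D, so f = 0.20·D and D = 0.082/0.20 = 0.41.

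Both exceed 0.07, 0.21, 0.28 and 0.38. Only 0.59 is larger.

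**5. Let the correlation be positive.** The article gives none, so this is a range of assumptions at N = 356, with sphericity for the interaction test. Entries are the detectable 12-month difference in SD.

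| ρ | interaction test, linear | interaction test, step | 1-df slope test |
|---|---|---|---|
| 0 | 0.46 | 0.41 | 0.38 |
| 0.25 | 0.40 | 0.36 | 0.33 |
| 0.5 | 0.33 | 0.29 | 0.27 |
| 0.75 | 0.23 | 0.21 | 0.19 |

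The slope column is 2.80 × 4 × √[((1 − ρ)/10) × (2/178)]. The smallest entry, 0.19, is 2.3 times 0.082.

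**6. Power for the earlier effects, read as 12-month SD differences** (interaction test, linear divergence):

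| Effect | 0.07 | 0.21 | 0.28 | 0.38 | 0.59 |
|---|---|---|---|---|---|
| ρ = 0 | 6 % | 20 % | 35 % | 61 % | 96 % |
| ρ = 0.5 | 8 % | 39 % | 65 % | 91 % | >99 % |

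**7. Face-value check.** Even with no conversion, 0.082 is not below the 1-year skills effect of 0.07.

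**8. Subsample N.** The share s with 12 months of data is not given; 50 to 90 % is assumed here. With the design effect recomputed, effective N = 1604s/[1 + (1604s/66 − 1) × 0.15]. With it held, as the article says, effective N = 1604s/4.495. The f column is the detectable f at ρ = 0.

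| s | recomputed: N | f | held at 4.495: N | f |
|---|---|---|---|---|
| 0.9 | 349 | 0.083 | 321 | 0.086 |
| 0.8 | 341 | 0.084 | 285 | 0.092 |
| 0.5 | 300 | 0.089 | 178 | 0.116 |

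**The case against.** The figure itself reproduces, so nothing was miscalculated, and calling an f of 0.082 very small by convention is defensible. That stands: the fault lies in the comparison and in what is concluded from it.

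The article never labels 0.082 as f, and the earlier study's metric is given only as an effect size, offered as a rough guide. Both readings are inferences. The first is strong, because the software, the design and the numerical match agree and a mean-difference reading fails. The second rests on the aim 1 text, which sets the same values beside a t-test effect and mean-difference benchmarks.

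A reader might infer that aims 2 and 3 are less sensitive than aim 1. The documents do not support that in general. It follows from the printed f, but with a correlation of 0.5 the interaction test detects 0.33 or 0.29 SD against aim 1's 0.298, and at 0.75 it detects 0.23 or 0.21 SD. Likewise, exceeding four of the five earlier effects describes the f as printed, not every plausible correlation.

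A reader might also infer that the plan assumed zero correlation and so contradicted its own-controls rationale. It states no correlation, and other epsilon and correlation pairs give the same 0.082.

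The planned linear random effects models may use a slope test and not the 4-df interaction test. The article does not say. A slope test is more sensitive under linear divergence, but not enough to rescue the comparison.

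Finally, the reuse of 356 is modest in effect if the design effect is recomputed, and no enrolment target was derived from 0.082.

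**Conclusion.** The point holds. The comparison of 0.082 with the earlier GTO effects is invalid as written, and the inference of sufficient power drawn from it is not supported. The printed f corresponds to about 0.41 to 0.46 SD at 12 months, assuming equal baselines and a step or linear time course. For correlations from 0 to 0.75 and either test, the detectable difference at N = 356 runs from 0.46 down to 0.19 SD.

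This does not show that the trial is underpowered for aims 2 and 3. That depends on a correlation, a model and a retained share that the article does not give. It shows that the stated argument does not demonstrate the promised 80 % power for effects as small as claimed.

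The carried-over N is a real inconsistency of secondary weight. Under the assumed 50 to 90 % retention, effective N is 300 to 349 with the design effect recomputed, and 178 at 50 % or 285 at 80 % with it held.

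**What to change.** In the Power analysis section, for aims 2 and 3:

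- Label 0.082 as Cohen's f and state the within-person correlation and epsilon entered.
- Restate the detectable effect as a 12-month difference in SD units and in days housed, for the planned model, over a range of correlations (for example 0, 0.25, 0.5 and 0.75).
- Give the expected number of Veterans with 12 months of data, and recompute the effective N and design effect for that subsample.
- Remove the comparison with the earlier study, or convert both sides to one scale.
- Keep the very-small description only if it is tied explicitly to the f convention.
- Revise the conclusion on power to match the restated figures.

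The cost is a rewrite of one paragraph and a less favourable stated figure. Design, allocation, data collection and tests are unchanged.
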